### Surgical correction of the spine

Dorsal lumbar access is achieved by a posterior lumbar skin incision along the midline. Paravertebral muscles are dissected away from bony structures taking care to achieve adequate hemostasis. Multi-level spinal osteotomies and/or releases of bony and ligamentous structures are performed to increase mobility of the spinal column. Bone grafts consisting of autologous bone or allograft are filled in to allow for bony fusion of the spinal column and limit motion. Pedicle screws are placed segmentally into vertebral bodies to provide adequate fixation of rod instrumentation. Stainless steel, titanium, or cobalt rods are placed to help correct and stabilize the spine while fusion occurs. Generally the greatest blood loss occurs during dissection and placement of pedicle screws while rod placement is associated with less blood loss. Subfascial Hemovac or Jackson-Pratt drains are placed at the wound site during closure to allow for adequate drainage and determination of post-operative blood loss.

### Investigation schedule and follow-up

Data will be collected pre-operatively regarding individual patient demographics, laboratory values, and the surgical procedure to be performed. Intra-operatively, data will be gathered to estimate blood loss and account for changes in fluid balance. Anesthesiologists are asked to maintain a MAP of 60 during the surgical exposure and anchor placement and a MAP of 70-90 during the surgical correction. Similarly, surgeons are asked to place only subfascial Hemovac drains at the incision site. These are both standard practice and have been shown by our group to help control blood loss during surgical exposure [21]. Postoperatively, laboratory values, drain output, and clinical outcomes are carefully followed until the patient is discharged. Given the increased risk of renal failure with the use of Aprotinin [7] changes in BUN to CR ratio are carefully monitored post-operatively. This data is recorded onto a de-identified data collection sheet by the researchers. These patient data sheets are then entered onto a protected electronic database, while the data sheets are stored as a back-up until the study is complete. Once the completed database is analyzed and summarized, the results will be presented to the involved participants without any identifiable patient information.

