**Methods/Design:**

Here we propose a prospective, randomized, double-blinded control study evaluating the effects of TXA, EACA, and placebo for treatment of adolescent idiopathic scoliosis (AIS), neuromuscular scoliosis (NMS), and adult deformity (AD) via corrective spinal surgery. Efficacy will be determined by intraoperative and postoperative blood loss. Other clinical outcomes that will be compared include transfusion rates, preoperative and postoperative hemodynamic values, and length of hospital stay after the procedure.

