**Discussion:**

The primary goal of the study is to determine perioperative blood loss as a measure of the efficacy of TXA, EACA, and placebo. Based on current literature and the mechanism by which the medications act, we hypothesize that TXA will be more effective at reducing blood loss than EACA or placebo and result in improved patient outcomes.

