### Physician Blinding

While clinicians are blinded to the patient's particular treatment group, at any time during surgery or in the post-operative period any clinician can be "unblinded" to the patient's treatment group if there is a concern for a complication. In addition, all patients are followed daily by the residents and fellows on the spine service and will also be followed by spine research fellows caring for the patient. The research residents also record and document basic metabolic profile (BMP) and complete blood count (CBC) lab values daily. The research fellows pay careful attention to the blood creatinine and blood urea nitrogen/creatinine ratio (BUN/Cr) monitoring daily for possible renal failure. Sequential compression devices (SCD) are given to all spine patients and they are encouraged to mobilize out of the hospital bed on post-op day 2. Spine patients are closely monitored for signs of a DVT by the medicine attending physicians and nurses caring for patients.

The anesthesiologist, surgeon, and researcher can be unblinded from the study at any time in the case of an apparent or suspected medical emergency. A copy of the consent form is placed in every chart in addition to a list of contact numbers of research persons involved with the study. There is also a note on the front cover of the chart informing all nurses and physicians that the patient is enrolled in the study with contact information for the research fellows and for the pharmacy department. The pharmacy is instructed to release the treatment group for any patient if requested by medical personnel caring for the patient or a spine research fellow. Order forms given to the pharmacy will be kept in a secure binder and will be made available upon request. As an additional resource, all physicians, anesthesiologists, and residents involved with patient care will have access to a sealed envelope with patient de-identified ID numbers and their assigned treatment groups.

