### Adverse events management

Complications include but are not limited to: suspected medication or allergic reaction, suspected myocardial infarction, stroke, deep vein thrombosis, pulmonary embolism, and renal failure. Other side effects that have been reported have been minor including headache, upset stomach, flushing, and hypotension. To date there has been no clear association between the use of anti-fibrinolytics, such as TXA and EACA, and renal failure or thrombosis [7,8]. A similar medication with anti-fibrinolytic properties, aprotinin, did lose FDA approval over concerns regarding renal failure in cardiac patients and the theoretical risk of thrombosis [9]. Aprotinin functions as a serine protease inhibitor. In contrast, TXA and EACA are synthetic lysine analogs that bind to and produce a structural change in plasminogen preventing conversion of plasminogen to plasmin and conversion of fibrinogen to fibrin. TXA and EACA therefore have a dual mechanism of anticoagulation: decreased fibrinolysis and decreased platelet aggregation due to the inactivation of plasmin. This difference in mechanism most likely accounts for the lack of association between the use of anti-fibrinolytics and renal failure [7,8]. Regardless, patients in the study are carefully monitored for signs of renal failure post-operatively. Any patient with an elevated or rising creatinine is carefully followed by resident and attending orthopaedic surgeons, internal medicine physicians, and the research fellows. If the elevation in creatinine is suspicious for renal failure, patients will be "unblinded" and treated appropriately. TXA and EACA have been used most in cardiac and spinal surgery and meta-analysis has clearly shown a reduction of intra-operative blood loss and allogenic transfusion rate with these medications [6-8,10,11,13].

Considering the reported reduction in operative blood loss and allogenic transfusion rate in both the cardiac and spine literature, the benefits of treatment outweigh the potential side effects. While these medications are widely used, they are currently not the standard of care in spinal surgery. This study aims to delineate the benefits of TXA versus EACA in spinal surgery, which may help to identify the patients most in need of this treatment. Complications will be diligently recorded and reported in the final manuscript.

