### Study Design

The study is designed as a prospective, randomized, double-blinded control trial. The patient, researcher, surgeon, and anesthesiologist will all be blinded to the patient's treatment. Patients will either receive TXA, EACA, or normal saline. The study will determine and compare differences in blood loss intra-operatively and estimate blood loss postoperatively through monitoring of subfascial Hemovac drain outputs at the incision site between the three groups. Postoperatively, laboratory values, drain outputs, and clinical outcomes will be carefully followed.

The primary goal of this study is to compare the efficacy of TXA to EACA to placebo in patients undergoing corrective spinal surgery for adolescent idiopathic scoliosis (AIS), neuromuscular scoliosis (NMS), and with adult deformity (AD). Outcome measures will include intra-operative and perioperative blood loss, transfusion rates, complete blood counts, and coagulation profiles, as well as postoperative wound drainage, complications, and length of stay.

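### Follow-up of clinical outcomes ends at discharge, so later complications are missed in every arm; the comparison is also biased if length of stay differs by arm

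*Protocol article*

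**What the plan says.** The article's section on investigation schedule and follow-up sets the end of observation: "Postoperatively, laboratory values, drain output, and clinical outcomes are carefully followed until the patient is discharged". Study Design lists the outcome measures, ending with "as well as postoperative wound drainage, complications, and length of stay". The abstract's Methods/Design paragraph names the outcomes to be compared besides blood loss as "transfusion rates, preoperative and postoperative hemodynamic values, and length of hospital stay after the procedure".

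Adverse events management lists the complications of interest as "suspected medication or allergic reaction, suspected myocardial infarction, stroke, deep vein thrombosis, pulmonary embolism, and renal failure" and promises that "Complications will be diligently recorded and reported in the final manuscript". It attaches no time window to them. The monitoring described under Physician Blinding is inpatient monitoring. On laboratory values it says "The research residents also record and document basic metabolic profile (BMP) and complete blood count (CBC) lab values daily", and clinical signs of deep vein thrombosis are watched for by the physicians and nurses caring for the patient.

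The abstract's Discussion hypothesizes that "TXA will be more effective at reducing blood loss than EACA or placebo and result in improved patient outcomes". It does not mention length of stay.

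**The concern.** Two separate things follow from a window that ends at discharge.

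The first is truncation, and it is unconditional. A deep vein thrombosis, pulmonary embolism, myocardial infarction, stroke or renal failure that occurs after the patient goes home falls outside the stated follow-up, whichever drug was given.

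The second is conditional. Length of stay is determined after randomization and is itself compared between arms. If it differs, one arm is watched for longer than another, and crude complication counts differ even when the drugs are equally safe. The statistical section (analysis of variance, regression, odds ratios) names no allowance for observation time.

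At stake is the safety side of the trial's message. The article argues that the benefits of treatment outweigh the side effects and undertakes to report complications. Those counts can be interpreted only if they cover a defined period that is the same in all arms.

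**Working it through.** **Is there a figure to reproduce?** No. The document gives no complication rate, no length of stay and no safety power. Only enrolment can be checked: 150 + 90 + 150 = 390, and 390 / 3 = 130 per arm at most. The sample sizes in Tables 2 and 3 concern blood loss and transfusion and do not bear on this point.

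**Assumptions for an illustration (none from the document).** A 30-day complication risk p of 3%, equal in both arms; stays of 5 to 7 days; event timing either at constant hazard or front-loaded. The 30-day horizon is only an example.

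**Share of 30-day events seen by day t.**
- Constant hazard: λ = −ln(1 − p)/30, share = (1 − e^(−λt))/p. With p = 0.03, λ = 0.001015. At t = 5 the risk seen is 0.00506 and the share is 0.00506/0.03 = 17%.
- Front-loaded with scale m days: F(t) = (1 − e^(−t/m))/(1 − e^(−30/m)). F(5) = 34% for m = 14, 52% for m = 7 and 81% for m = 3.

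So discharge at day 5 would lose between 19% and 83% of 30-day events, depending on timing.

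**Apparent risk ratio with no true effect** = share seen in the shorter-stay arm / share seen in the longer-stay arm.

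| Stay, days | Constant hazard | m = 14 | m = 7 | m = 3 |
|---|---|---|---|---|
| 5 vs 5 | 1.00 | 1.00 | 1.00 | 1.00 |
| 5 vs 6 | 0.83 | 0.86 | 0.89 | 0.94 |
| 5 vs 7 | 0.715 | 0.76 | 0.81 | 0.90 |

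**Against sampling error, 130 per arm, 5 vs 6 days.** The standard error of the log risk ratio is √[(1 − a)/(130a) + (1 − b)/(130b)], where a and b are the risks seen.
- Constant hazard: a = 0.00506, b = 0.00607, so expected events are 0.66 and 0.79. SE = 1.66, and the 95% limits lie a factor e^(1.96 × 1.66) ≈ 26 either side.
- Front-loaded, m = 3: a = 0.0243, b = 0.0259, so expected events are 3.2 and 3.4. SE = 0.773, a factor of about 4.5 either side.

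The distortion itself is a factor of 1/0.83 = 1.20 in the first case and 1/0.94 = 1.06 in the second.

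**With a fixed common window.** The null risk ratio is 1.00 whatever the stay. At 3% risk the expected events per arm are 130 × 0.03 = 3.9, against about 0.7 with discharge at day 5 under constant hazard. Power stays low. For an assumed 3% vs 6%, two-sided 5%, the null SE is √(2 × 0.045 × 0.955/130) = 0.0257 and the alternative SE is √[(0.03 × 0.97 + 0.06 × 0.94)/130] = 0.0256. Power = Φ[(0.03 − 1.96 × 0.0257)/0.0256] ≈ 21%. It falls to about 11% if 40% of events are captured and 7% if 20% are.

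**The case against.** The strongest reply is that this is a condensed article, that the adverse-event section gives complications no window, and that the full protocol may set one. The silence of that section is real. But the follow-up section does not leave the matter open: it states an end point for clinical outcomes, and Study Design lists complications among the outcome measures. Reading the two together is natural. If another window was intended, the text should say so.

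Other objections succeed against stronger readings that a reader might infer:

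- *The comparison is biased as it stands, because treatment shortens stay.* The document does not say that stay will differ by arm. It lists stay as an outcome and hypothesizes better patient outcomes with TXA in general terms. With equal stay there is no bias from this source.
- *An antifibrinolytic will be made to look safer.* A shorter stay would hide late events, but a complication can itself prolong stay and so extend its own observation. The net direction cannot be determined from the document.
- *Renal failure is poorly captured.* Creatinine and the BUN/Cr ratio are followed daily in hospital, so renal events arising there are seen. Only later ones are lost.
- *Drain output shares the bias.* The document does not say that drains stay in until discharge. Output can be recorded only while a drain is in place, so nothing shows that stay sets the drainage window. Blood loss is also to be calculated from body mass, hematocrit and fluid balance. This reading is not supported.

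It is also fair to object that, with few events, a fixed window will not make the safety comparison well powered. That is true, but it is no reason to discard events that could be counted at little cost.

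**Conclusion.** The point holds in a limited form. Under the stated follow-up, complications after discharge are missed in all arms, and this does not depend on any difference in stay. The share lost is unknown; under the assumptions shown, with discharge at day 5, it runs from about a fifth to about five sixths of 30-day events.

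Bias between arms is conditional on stay differing, and its direction is open. In the simple case without feedback from complications to stay, 5 vs 6 days gives an apparent risk ratio of about 0.83 to 0.94. That is small beside the sampling error with at most 130 per arm. All these figures rest on assumed stays, risk and timing; the document supplies none of them.

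This is a cheap improvement to the safety reporting. It is not a flaw that threatens the blood-loss comparison.

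**What to change.** In the section on investigation schedule and follow-up, state that the complications listed under Adverse events management are counted to one fixed postoperative day in every patient, the same in all three arms. Thirty days is only an example; the investigators should choose the day. Take events after discharge from the chart or a return contact, and record for each patient whether follow-up to that day was complete. Keep length of stay as a separate outcome.

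The cost is one more item on the data sheet, with no extra procedure. The document describes no routine return visit, so patients without a return contact will have some late data missing, and the number of such patients should be reported by arm.

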### Statistical considerations

While useful, this analysis is limited by the great variability in study design and control groups between prior orthopedic studies. Since no orthopedic study has compared TXA and EACA together, conducting a power analysis required pooling of data from two or three studies. This proved difficult, as control groups were dissimilar between the studies (Table 2).

Power analysis was performed multiple times using data from several studies. When estimating the sample size required comparing TXA and EACA, attempts were made to choose two studies with similar intra-operative blood losses within the control groups. A cardiac study, albeit with dissimilar sample variance, was also used to estimate the sample size needed for this study. Finally, determining the sample size for outcomes of total blood loss and transfusion requirements proved difficult as even fewer studies reported these outcomes. Blood loss will be estimated in the operation room, but will also be calculated taking into account patient body mass, pre/postoperative hematocrit, and relative fluid balance [21-23]. This will minimize the variance in reported blood loss. A power analysis will be performed again once 60 patients with AIS, NMS, or AD have been enrolled into the study.

With a single institution of surgeons and anesthesiologists participating in the study, we expect a smaller variation in operative blood loss than reported in prior studies. Data will not only be analyzed for all patients collectively, but will also be stratified by diagnosis (AIS, NMS, and AD). The purpose of stratifying into these groups is threefold. First, separation by diagnosis allows for more diligent control of patient-related factors that may affect blood loss and transfusion rate. Secondarily, stratification by diagnosis allows for a better understanding of which patients benefit most from one treatment option over another. Lastly, it allows for a broader application of the results from this study not only to patients with AIS, but to all spinal deformity patients.

An analysis of variance, univariate, and multivariate logistic regression analysis will be used to analyze the difference in outcomes. Odds ratios will be calculated regarding the risk for autologous or allogenic transfusion both intra and postoperatively. P-values will be calculated regarding the relative blood loss in the intra and postoperative periods as well. The groups will be analyzed to characterize the homogeneity of their pre-operative characteristics that may influence blood loss. Patients with AIS, NMS or AD will be stratified by primary diagnosis and analyzed separately but also collectively accounting for patient and surgery-related confounders. Non-continuous data will be analyzed with a non-parametric test. Pre-operative curve characteristics including Cobb angle and number of vertebrae fused will be categorized to ensure similar groups for comparison.

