**NMS**	
Inclusion	Exclusion
1. Between 10 and 80 years of age	1. Congenital and syndromic scoliosis
	2. Previous corrective spinal surgery that is being revised

The maximum total number of patients enrolled will be 150 of AIS (50 in each treatment arm), 90 for NMS (30 in each treatment arm), 150 for AD (50 in each treatment arm). These numbers were estimated by critically reviewing the existing spine and cardiac literature comparing TXA and EACA against placebo [6-20]. A power analysis was conducted using the literature to determine the number of patients necessary to attain significant results (Tables 2 and 3).

**Table 2 T2:** Power study to determine number of patients needed in AIS group.

	TXA		Amicar		Control		
	**Blood loss**	**Standard Deviation**	**Blood Loss**	**Standard Deviation**	**Blood Loss**	**Standard Deviation**	**Sample Size Needed**

Intra-op blood loss	1072 mL	+/- 425 mL	-	-	1420 mL	+/- 644 mL	58

Intra-op blood loss	1072 mL	+/- 425 mL	893 mL	+/- 220 mL	-	-	80

Total blood transfused	1253 mL	+/- 884 mL	-	-	1784 mL	+/- 733 mL	55

Total units transferred	-	-	1.2 U	+/- 1.1 U	2.2 U	+/- 1.3 U	34

**Table 3 T3:** Power study to determine number of patients needed for NMS group

	TXA		Amicar		Control		
	**Blood loss**	**Standard Deviation**	**Blood Loss**	**Standard Deviation**	**Blood Loss**	**Standard Deviation**	**Sample Size Needed**

Intra-op blood loss	1408 mL	+/- 605 mL	-	-	2690 mL	+/- 1266 mL	14

Intra-op blood loss	1976 mL	+/- 860 mL	1117 mL	+/- 718 mL	-	-	30

Total blood transfused	808 mL	+/- 531 mL	-	-	1391 mL	+/- 723 mL	34

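### Stratifying by diagnosis is meant to show who benefits most, but neither stated analysis compares treatment effects between AIS, NMS and AD

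*Protocol article*

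**What the plan says.** Statistical considerations gives three purposes for stratifying by diagnosis. The second is that "stratification by diagnosis allows for a better understanding of which patients benefit most from one treatment option over another".

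The same section states the analysis: "Patients with AIS, NMS or AD will be stratified by primary diagnosis and analyzed separately but also collectively accounting for patient and surgery-related confounders". The methods are named in one sentence: "An analysis of variance, univariate, and multivariate logistic regression analysis will be used to analyze the difference in outcomes". Odds ratios are planned for transfusion. For blood loss the text says "P-values will be calculated regarding the relative blood loss in the intra and postoperative periods as well".

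Patient selection sets maximum enrolment at 50 per arm for AIS, 30 for NMS and 50 for AD. Power tables are given for AIS (Table 2) and NMS (Table 3), but not for AD.

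The article nowhere names a treatment-by-diagnosis interaction, a test of heterogeneity, or a direct contrast of treatment effects between diagnoses.

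**The concern.** Asking which patients benefit most means asking whether the treatment effect differs between diagnoses. A separate analysis asks whether there is an effect within one diagnosis. A collective analysis adjusted for confounders, even with diagnosis among them, estimates one common effect. Neither answers the stated question.

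Without a direct comparison, the results at hand would be three sets of P-values from cohorts of different size and probably different variance. A pattern such as significant in AIS but not in NMS is easily taken as evidence that AIS patients benefit more. With 30 per arm in NMS against 50 in the others, that pattern arises often when the effect is the same everywhere.

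The aim is more than a passing remark. The Adverse events management section hopes the study will help identify the patients who most need treatment. The Discussion suggests that the heavier bleeding in NMS may enlarge the difference between tranexamic acid (TXA) and epsilon aminocaproic acid (EACA), which is itself a hypothesis of effect modification.

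**Working it through.** The plan gives no figure for a comparison between diagnoses, so there is none to reproduce. The point does not rest on the sample sizes in Tables 2 and 3; only their means and standard deviations (SDs) are used.

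**Inputs**
- Per-arm sizes 50 (AIS), 30 (NMS), 50 (AD): Patient selection.
- AIS, TXA vs control, intra-operative blood loss 1072 (SD 425) vs 1420 (SD 644) mL: Table 2.
- AIS, TXA vs EACA, 1072 (SD 425) vs 893 (SD 220) mL: Table 2.
- NMS, TXA vs control, 1408 (SD 605) vs 2690 (SD 1266) mL: Table 3.
- Assumed: two-sided 0.05 (level and sidedness are not stated), full enrolment, independent cohorts, normal approximation, and the same SMD in all three diagnoses, including AD, which has no table.

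**Step 1: standardised effects**, SMD = difference / √((SD₁² + SD₂²)/2)
- TXA vs control: 348 / 545.6 = 0.64
- TXA vs EACA: 179 / 338.4 = 0.53

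**Step 2: power per diagnosis**, Φ(SMD/√(2/n) − 1.96); the opposite tail is negligible at these effects. √(2/50) = 0.200 and √(2/30) = 0.258.
- SMD 0.64 (unrounded 0.638): 3.19 − 1.96 gives 89% at n = 50; 2.47 − 1.96 gives 70% at n = 30.
- SMD 0.53 (unrounded 0.529): 2.64 − 1.96 gives 75% at n = 50; 2.05 − 1.96 gives 54% at n = 30.

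**Step 3: chance that the three diagnoses disagree in significance**, 1 − p₁p₂p₃ − (1−p₁)(1−p₂)(1−p₃)

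| Common true effect | Power AIS / NMS / AD | All significant | None | Disagree |
|---|---|---|---|---|
| SMD 0.64 | 89 / 70 / 89% | 55% | 0.4% | 45% |
| SMD 0.53 | 75 / 54 / 75% | 30% | 3% | 67% |
| SMD 0.50 | 71 / 49 / 71% | 24% | 4% | 71% |
| SMD 0.30 | 32 / 21 / 32% | 2% | 36% | 62% |
| None | 5 / 5 / 5% | 0% | 86% | 14% |

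**Step 4: sensitivity**
- The same absolute effect of 348 mL, with the table SDs (545.6 for AIS, 992.2 for NMS) and the AIS SD assumed for AD: NMS power is Φ(348/(992.2 × 0.258) − 1.96) = 27%. Power is then 89 / 27 / 89% and disagreement 77%.
- One-sided 0.05 (1.645 in place of 1.96): at SMD 0.64, power is 94 / 80 / 94% and disagreement 30%; at SMD 0.53, power is 84 / 66 / 84% and disagreement 53%.

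**Step 5: what a direct test does.** A heterogeneity test across the three diagnoses for one treatment contrast (Cochran Q, 2 df, 20,000 simulated trials, common SMD 0.64) declares a difference in 4.9% of trials, as it should at the 5% level.

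**Step 6: power of that comparison.** The SMD difference detectable with 80% power is (1.96 + 0.84) × its standard error.
- AIS vs NMS: 2.80 × √(2/50 + 2/30) = 2.80 × 0.327 = 0.91
- AIS vs AD: 2.80 × √(4/50) = 2.80 × 0.283 = 0.79

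Both exceed the AIS effects of 0.53 to 0.64 from Step 1.

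**The case against.** The strongest reply is that this is detail a condensed article leaves to a fuller plan. The collective analysis and the regression methods named could carry an interaction term, and an unseen analysis plan may include one. That is possible, but the article states both the inference and the analysis meant to support it, and as written the two do not match. A fuller plan containing the test would be correcting this text.

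A reader might infer that the investigators will compare P-values across diagnoses and call the difference a difference in benefit. The article does not say so. It says only that stratification aids understanding, and it plans odds ratios as well as P-values. What stands is that the stated analyses leave room for that misreading. Nor are the disagreement rates rates of false claims, since a false claim also requires someone to draw the faulty inference.

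A reader might also take the tables as showing that the effect really differs, because TXA lowers blood loss by 348 mL in AIS and 1282 mL in NMS. These are figures from the literature, and Statistical considerations warns that control groups were dissimilar between the source studies. Heavier bleeding in NMS does not by itself explain the gap either: the relative reductions are 1 − 1072/1420 = about 25% and 1 − 1408/2690 = about 48%. The rows say nothing reliable about effect differences within this trial.

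Two further objections are fair. Separate analyses are legitimate for the question of whether treatment works within each diagnosis, and the diagnoses have their own enrolment targets. The interaction test would also be weak, as Step 6 shows. That limits what the trial can say about who benefits most, but it does not make separate P-values an answer to that question.

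**Conclusion.** The point holds as a mismatch between a stated purpose of the stratification and the stated analyses. It does not touch the primary comparison of TXA, EACA and placebo, and it does not show that a false subgroup claim will be made.

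If the effect is identical in all three diagnoses, disagreement in significance is a common outcome: about 45% at SMD 0.64 and about 67% at SMD 0.53. These figures rest on the assumptions listed with the inputs; the SMDs come from AIS literature data, and applying them to AD is pure assumption. One-sided testing at 0.05 would lower the figures to about 30% and 53%, and a common absolute effect with the larger NMS SDs would give 77%. The conclusion is the same throughout this range.

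**What to change.** Add a treatment-by-diagnosis interaction to the collective model already planned. With three treatments and three diagnoses this has (3 − 1) × (3 − 1) = 4 degrees of freedom. Report the treatment effects in each diagnosis, and the differences in effect between diagnoses, with confidence intervals. State that any claim about which patients benefit most will rest on the interaction and those intervals, not on separate P-values, and label it exploratory.

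The cost is one model term and some extra reporting, with no more patients. The drawback is low power, so the plan should also say that a non-significant interaction is not evidence of equal benefit. Analysing blood loss on a log scale, so that effects are ratios, is an option but not a required part of the change.

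### Blood loss has no suitable adjusted model, and ANOVA contrasts with a common error term would misstate precision if arm SDs differ as in Table 2

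*Protocol article*

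**What the plan says.** The Abstract of the protocol article sets the target: "The primary goal of the study is to determine perioperative blood loss as a measure of the efficacy of TXA, EACA, and placebo". Tables 2 and 3, under Patient selection, plan for it in mL.

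Statistical considerations names the methods in one sentence for all outcomes: "An analysis of variance, univariate, and multivariate logistic regression analysis will be used to analyze the difference in outcomes". It then adds:

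- for transfusion: "Odds ratios will be calculated regarding the risk for autologous or allogenic transfusion both intra and postoperatively";
- for blood loss: "P-values will be calculated regarding the relative blood loss in the intra and postoperative periods as well";
- for other data types: "Non-continuous data will be analyzed with a non-parametric test";
- for the diagnosis groups, that they will be "analyzed separately but also collectively accounting for patient and surgery-related confounders";
- for baseline curve data: "Pre-operative curve characteristics including Cobb angle and number of vertebrae fused will be categorized to ensure similar groups for comparison".

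Of the methods named, ANOVA is the one that compares means of a continuous outcome, so blood loss falls to it. The section does not say whether the ANOVA is classical or Welch, or which error term pairwise contrasts use.

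**The concern.** Two things are at stake.

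First, the promised adjustment has no model for the main outcome. Logistic regression needs a binary outcome. It serves transfusion, but cannot express a treatment effect on blood loss in mL after allowing for confounders. Cobb angle and number of vertebrae fused are to be categorized to check that groups are similar. Yet the Background lists deformity severity and number of vertebrae fused among the factors affecting blood loss, so they are natural covariates.

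Second, classical ANOVA assumes one variance for all arms, and its usual pairwise contrasts share one error term. In Tables 2 and 3 the control arm has by far the largest SD. If that holds in the trial, control-arm variance inflates the standard error of TXA against EACA, the comparison that the article says is missing from the orthopedic literature. The contrasts with control would then look more precise than they are.

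**Working it through.** **Inputs.** Intra-operative blood loss, mean (SD) in mL.

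- AIS, Table 2, 50 per arm: TXA 1072 (425), EACA 893 (220), control 1420 (644).
- NMS, Table 3, 30 per arm: TXA SD 605 in one row and 860 in another, EACA SD 718, control SD 1266.
- AD: no planning table, so nothing can be computed.
- Assumed: normal data, two-sided 5% tests without multiplicity adjustment. The article states no alpha, sidedness or power.

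**The plan's own figures.** Table 2 ("Power study to determine number of patients needed in AIS group") gives 58 for TXA–control and 80 for TXA–EACA. Take n per arm = 2 × [SD × (1.645 + 0.842) / difference]², with SD the simple mean of the two arm SDs, one-sided 5% and 80% power (both assumed):

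- TXA–control: SD 534.5, difference 348, n = 29.17, total of two arms 58.3.
- TXA–EACA: SD 322.5, difference 179, n = 40.14, total of two arms 80.3.

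Both stated figures are reproduced as two-arm totals. Not every other row follows this rule (Table 3, TXA–EACA: 20.9 against a stated 30). What matters here is that planning went pair by pair, using only the two arms compared.

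**Standard errors, AIS.** Common error variance = (425² + 220² + 644²)/3 = 214,587, so the common SD is 463.2 mL. Every contrast then has SE = 463.2 × √(2/50) = 92.6 mL. The unequal-variance SE is √[(s₁² + s₂²)/50]. Type I error and power come from 50,000 simulated trials, with 3n − 3 = 147 degrees of freedom for the common-error contrasts.

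| AIS contrast | Common SE | Unequal-variance SE | Ratio | Type I error, common | Power, common / Welch |
|---|---|---|---|---|---|
| TXA–EACA | 92.6 | 67.7 | 1.37 | 0.8% | 48% / 74% |
| TXA–control | 92.6 | 109.1 | 0.85 | 9.5% | 93% / 88% |
| EACA–control | 92.6 | 96.2 | 0.96 | 5.9% | above 99% / above 99% |

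Check by formula: type I error for TXA–control = 2 × P(Z > 1.976 × 92.6/109.1) = 9.3%; power for TXA–EACA = P(Z > (1.976 × 92.6 − 179)/67.7) = 48%. Welch type I error is 4.9% to 5.0% for all three contrasts. The overall F test has type I error 6.0%.

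**NMS, 30 per arm.** The two figures are for TXA SD 605, then 860.

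- Common SE: 235.0, 252.0 mL.
- TXA–EACA: 171.4, 204.5 mL; ratio 1.37, 1.23.
- TXA–control: 256.2, 279.4 mL; ratio 0.92, 0.90; type I error 7.3%, 7.9%.
- EACA–control: 265.7 mL in both; ratio 0.88, 0.95; type I error 8.3%, 6.5%.
- Overall F: type I error 5.9%, 5.8%.

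At the Table 3 means with TXA SD 860, TXA–EACA power is 96% with the common error against 98% with Welch. The assumed difference (1976 − 1117 = 859 mL) is so large that little power is lost.

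**How far this depends on the SDs.** With equal arm SDs every ratio is 1.00. With one assumed CV of 0.43 in each AIS arm, the TXA–EACA ratio is √{[(1072² + 893² + 1420²)/3] / [(1072² + 893²)/2]} = 1.17, and power is about 42% against 55% with Welch.

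**The case against.** The strongest reply has four parts.

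- **The SDs are not from this trial.** They are literature values from separate studies. Statistical considerations says that control groups were dissimilar and that less variation is expected here. Table 3 carries two TXA SDs, so between-study differences are mixed with any arm effect. This stands: a reader might infer that the trial's standard errors will be wrong, but the document does not show that arm variances will differ. The expected smaller variation settles nothing either way, since shrinking all SDs in proportion leaves the ratios unchanged.
- **The common error term is not stated.** This also stands. It is the default in ANOVA, but separate two-arm tests would avoid the problem, and with equal arms the overall F test barely moves.
- **Logistic regression is meant for transfusion.** A reader might infer that blood loss will be dichotomized. The text does not say so; it ties odds ratios to transfusion. The gap in the adjusted analysis of blood loss remains.
- **Such detail belongs in the analysis plan, which is not shown.** In part. The ANOVA variant and error term could be settled there. But the article does name its methods, and among them no multivariable model fits a continuous outcome.

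Two further inferences fail. SDs rising with means might suggest a log scale as the main analysis, but the EACA CVs are 220/893 = 0.25 and 718/1117 = 0.64, against 0.40 to 0.47 for TXA and control. And no gain in sample size from covariates can be claimed, because the document gives no R².

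**Conclusion.** The point holds in a limited form. The firm part is that the article promises a confounder-adjusted collective analysis and names only a logistic model, which cannot give an adjusted difference in mL for its main outcome.

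The numerical part is conditional on common-error contrasts and on arm SDs as tabulated. In AIS it would cost the head-to-head comparison about 26 percentage points of power (48% against 74%) and raise type I error for TXA–control to about 9%. The power loss is the sturdier of the two: if SDs merely follow means, arms with no treatment effect would have equal SDs and type I error would stay near 5%. In NMS the standard errors err in the same directions, but head-to-head power hardly changes. This is a worthwhile improvement in method, not a flaw that invalidates the design.

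**What to change.** State the analysis by outcome type:

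- **Blood loss:** compare arms by Welch contrasts or by a linear model with heteroscedasticity-robust standard errors. Include arm, diagnosis (in the collective analysis) and pre-operative covariates already collected, such as body mass, hematocrit, Cobb angle and planned levels, in continuous form. Keep mL as the main scale, matching Tables 2 and 3, with a log-scale analysis as a sensitivity check only.
- **Transfusion yes/no:** keep logistic regression and odds ratios.

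The cost is a change of wording, slightly more analysis work and a negligible loss of degrees of freedom. No extra patients or data are needed. If arm SDs prove equal, almost nothing is lost.
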